## Background

Childhood obesity has been high on the public health agenda for two decades now and while the rapid increase in prevalence seen in the 1990s in the Nordic countries seems to have levelled off to about 3% in Sweden at the population level [1], huge social inequalities persist [2]. According to data from all 4-year-olds in Stockholm County born in 2012, collected through child health care services, the obesity prevalence varies from zero in the most well-off area to over 5% in the most disadvantaged [3]. The explanation for this gradient in younger children does not seem to be due to lower physical activity [4], but can to a large extent be explained by more unhealthy dietary habits in families with low levels of education [5] and of non-Nordic origin [6]. In adolescents, overweight and obesity often result in body image dissatisfaction, poorer self-assessed health status, social isolation, and decreased life satisfaction [7]. In addition, in high-income countries a negative association exists between educational attainment and obesity, particularly in women [8]. Although children in pre-school age [9] and early school-age [10] seem to be adequately physically active there is a clear decrease in physical activity with increasing age [11]. Evidence from Sweden [10, 12, 13] and elsewhere [14] suggest that children are less physically active in the home environment, e.g. during weekends.

When it comes to adults, higher rates of obesity and low physical activity are found in groups with low socio-economic position (SEP), and it has been speculated that these factors are the main causes behind the higher prevalence and earlier onset of type-2 diabetes (T2D) among adults with low SEP [15]. Furthermore, studies have shown that immigrants to Sweden have a significantly higher risk of T2D than Swedish-born individuals even when adjusted for established risk factors [16]. Today it is recognised that development of both obesity and T2D is driven by interacting genetic and environmental factors and is preventable to a large extent [17]. Because health-related behaviours and obesity often track from childhood to adulthood [18, 19], interventions should start from an early age and target the whole family.

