### The intervention

According to the typology of Benach et al. [39], the Healthy School Start Plus programme can be typed as a universal intervention with additional focus on the health gap. It will benefit all children in participating schools but due to the flexibility of the intervention components, extra attention can be given to families with higher needs. Based our previous experiences with the Healthy School Start programme, we added a fourth intervention component to the three existing ones. The four components are: 1) A health information brochure to parents; 2) one or two MI sessions with parents according to family needs and performed by the school nurse; 3) nine classroom activities performed by teachers with home assignments to be completed by children together with their parents; and 4) a web-based self-test of T2D risk for parents with feedback concerning the level of risk. Parents with an elevated risk will be encouraged via the website to visit primary health care for a health consultation according to existing procedures including testing, counselling and yearly follow-up, if diabetes or pre-diabetes is established. In this way, we hope to motivate high-risk families to improve health-related behaviours for the whole family.

Table 1 presents the programme theory of the Healthy School Start Plus study including intervention characteristics, process and outcome evaluation variables.

**Table 1 Tab1:** Programme theory of A Healthy School Start Plus intervention study

Intervention characteristics				Process evaluation		Outcome evaluation	
Input	Core intervention components	Materials	Implementation strategies	Mediators	Process outcomes	Short term outcomes	Long term outcomes
Expert support Local capacity Funding	Health information MI with parents Classroom lectures and home assignments Parent’s test for T2D	Health brochure Teacher’s manual Child’s workbook	Written agreement with schools Kick-off meeting in schools Training of school nurses in MI Instructions for teachers in class room component	Parental self-efficacy Parental behavioural capability Parental outcome expectations and expectancies Child observational learning Motivation	Dose Fidelity to intervention components Feasibility Acceptability Context	Intake of vegetables and fruit Intake of unhealthy foods Physical activity Sedentary behaviour	BMI in children with overweight and obesity Waist circumference in children with overweight and obesity

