### Data analysis

A detailed statistical analysis plan will be developed in collaboration with an academic statistician prior to the start of the data analysis. Here we describe the key elements. Differences in continuous demographic variables at baseline between intervention and control group will be presented as means ± SD and tested using independent t-tests for normally distributed data. Non-normally distributed variables will be presented as median and range and will be analysed by non-parametric tests. For categorical variables, proportions will be presented and differences will be analysed by chi-square test. Effectiveness with regard to primary and secondary outcomes will be analysed by mixed-effect regression analyses with two levels (individual and school) with data at T1 or T2 as outcomes, according to the principle of intention to treat. We will first test a crude model for all outcomes at T1 or T2 with group as the predictor and adjusted for baseline values of the relevant outcome. In a second step, sex and parental SEP will be added to the model. Interaction between group and sex or group and parental SEP will be tested and analyses stratified if significant interaction terms are found. All children with measurements at T0 will be included and missing data will be handled with multiple imputation. The effect that any missing data might have on results will be assessed by performing sensitivity analyses of augmented data sets. Analysis will also be performed per protocol including only those children whose parents have attended at least one MI session.

Subgroup analyses will be performed with regard to baseline BMI status (underweight plus normal weight, overweight, obesity) and waist circumference (dichotomised). In addition quantile regression will be performed to detect differential intervention effects according to baseline BMI quartiles. The hypothesis behind the subgroup analysis is that children with a high BMI at baseline will respond with a decrease in BMI in contrast to children with lower BMI. Regarding physical activity (TPA, MVPA and time spent sedentary) outcomes will be adjusted for accelerometer monitor wear time.

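### Quantile regression is assigned to find intervention effects by baseline BMI quartile, which it does not estimate, and no test of the high-versus-lower BMI contrast is named

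*Protocol article*

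**What the plan says.** All of this is in the protocol article, mainly under Data analysis.

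- **Hypothesis.** The subgroup analysis rests on the expectation that "children with a high BMI at baseline will respond with a decrease in BMI in contrast to children with lower BMI". That is a comparison between groups defined at baseline.
- **Subgroups.** "Subgroup analyses will be performed with regard to baseline BMI status (underweight plus normal weight, overweight, obesity) and waist circumference (dichotomised").
- **Additional method.** "In addition quantile regression will be performed to detect differential intervention effects according to baseline BMI quartiles".
- **Interaction tests named.** "Interaction between group and sex or group and parental SEP will be tested and analyses stratified if significant interaction terms are found". Baseline BMI and waist circumference are not in this list.
- **Main model.** "mixed-effect regression analyses with two levels (individual and school) with data at T1 or T2 as outcomes", with the crude model adjusted for the baseline value of the outcome concerned.
- **Place of BMI in the trial.** BMI is a secondary outcome. Table 1 lists "BMI in children with overweight and obesity" among the long-term outcomes.

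The article gives key elements only and says that a detailed statistical analysis plan will follow. That plan is not at hand.

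**The concern.** Two different questions are treated as one. The first is whether the intervention effect differs between children who start with high and low BMI. That is effect modification by a baseline covariate, and it is what the hypothesis states. The second is whether the effect differs between the upper and lower parts of the distribution of follow-up BMI. Quantile regression answers the second.

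With baseline BMI in the model, an upper quantile refers to children whose follow-up BMI is high for their starting value. It does not refer to children who started high. A result read as the article describes it could therefore hide a real response among heavier children, or suggest one that has nothing to do with starting BMI.

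The hypothesis is also comparative, and the article names no test of that comparison. If the contrast is judged by whether one BMI subgroup reaches significance and another does not, the answer depends largely on subgroup size.

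**Working it through.** The plan gives no figure for this analysis, so there is none to reproduce. The sample size concerns the dietary outcome and is untouched: 99 per arm for a difference of 0.8 with SD 2.0 gives 198, and 198 × [1 + 14 × 0.02] = 253.4, rounded up to 17 × 15 = 255.

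**Step 1: what the named method estimates.** Let *g* be group, *b* baseline BMI sds and *y* follow-up BMI sds. All inputs here are assumptions, not document figures: *b* standard normal, *y* = 0.9*b* + *e*, *e* with SD 0.4, clustering ignored, and 30,000 simulated children, so that sampling error is negligible. The fitted model is the quantile regression of *y* on *g* and *b*.

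*Scenario A.* The true effect is -0.30 in the top baseline quartile and 0 elsewhere.

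| Quantile of *y* | 0.125 | 0.25 | 0.5 | 0.75 | 0.875 |
|---|---|---|---|---|---|
| Adjusted for *b* | -0.079 | -0.078 | -0.074 | -0.065 | -0.057 |
| Not adjusted for *b* | 0.014 | 0.011 | -0.010 | -0.131 | -0.219 |

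The adjusted estimates lie near the overall mean effect, 0.25 × -0.30 = -0.075, at every quantile, and are smallest at the top. The unadjusted ones follow the baseline pattern in part, because BMI tracks over time, but do not reach -0.30.

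*Scenario B.* The effect is -0.30 only where *e* > 0.27, about a quarter of children at any baseline BMI. The true effect is about 0.25 × -0.30 = -0.075 in every baseline quartile.

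| Quantile of *y* | 0.125 | 0.25 | 0.5 | 0.75 | 0.875 |
|---|---|---|---|---|---|
| Adjusted for *b* | 0.008 | 0.005 | -0.012 | -0.129 | -0.228 |

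Read as effects by baseline quartile, this would be a false finding that heavier children respond.

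**Step 2: what does recover the pattern.** A linear model with group × baseline-quartile terms, in scenario A, gives interactions against the lowest quartile of 0.011, 0.007 and -0.298. A purely linear group × *b* term does not. Its group coefficient is -0.075 and its slope is -0.30 × 0.318 = -0.095, where 0.318 is the normal density at the upper quartile. At the quartile medians (*b* = -1.15, -0.32, 0.32, 1.15) the fitted effects are +0.03, -0.04, -0.11 and -0.18, against true values of 0, 0, 0 and -0.30.

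**Step 3: separate significance is not a test of the contrast.** Take 352 children, residual SD 0.4, the same true effect in both BMI groups (0.10 to 0.20 sds) and a high-BMI share of 15% to 25%. All but the 352 are assumed. The SE in a subgroup of *n* children is 0.4 × √(4/*n*). At a 20% share and an effect of 0.15, *n* = 70.4 and 281.6, and power is 0.35 and 0.88. The chance that exactly one subgroup is significant is 0.35 × 0.12 + 0.88 × 0.65 = 0.61 (0.62 before rounding). Over the whole range this chance is 36% to 68%, with no true difference between the groups.

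**Step 4: precision of the interaction.** The SE of the contrast relative to the SE of the overall effect is √(1/*s* + 1/(1 − *s*)) for share *s*: 2.8 at 15%, 2.5 at 20% and 2.3 at 25%.

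**The case against.** The article ties the hypothesis to the subgroup analyses and adds quantile regression only as a supplement. Estimates by baseline BMI group do bear on the hypothesis. In scenario A, estimates within baseline strata would show the pattern, and the Table 1 outcome concerns children with overweight and obesity, whom such estimates describe directly. This stands. A reader might infer that the hypothesis goes untested altogether, and the article does not support that.

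The article also lists no covariates for the quantile regression; baseline adjustment is stated for the mixed models. Without adjustment the method partly follows the baseline pattern. With explicit group × baseline-quartile terms a median regression recovers the contrast (-0.286 in scenario A). This stands as a limit on the size of the problem. However, no such term is described, and if one were added the interaction would do the work, not the choice of quantile regression.

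The absence of a BMI interaction could be detail left to the analysis plan. That is partly right, and the unseen plan may supply one. The article does, however, name the interactions to be tested and leaves out the one that its own hypothesis calls for.

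Two further inferences are tempting but unsupported:

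- **The school effect is dropped.** The article does not say how the quantile regression treats clustering, nor that the BMI subgroups are fitted separately.
- **The obesity subgroup is too small to analyse.** The article gives no obesity prevalence for this sample. The Background figure, "the obesity prevalence varies from zero in the most well-off area to over 5% in the most disadvantaged", concerns 4-year-olds in Stockholm County, whereas these are six-year-olds in schools selected on parental education.

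**Conclusion.** The point holds, at moderate severity. The quantile-regression sentence assigns the method a task that it does not perform. This follows from the definition of the method and does not depend on the simulation inputs. The size of the possible error does depend on them: under the stated assumptions, a true -0.30 appears as -0.06 to -0.08 throughout, and a flat -0.075 appears as a gradient from 0.01 to -0.23. These figures apply to a baseline-adjusted fit, and an unadjusted fit is less far off.

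The second part also holds: the subgroup estimates address the hypothesis, but the article names no test of the contrast that the hypothesis states. The consequences are confined to an exploratory analysis of a secondary outcome. The primary dietary comparison and the sample size stand.

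**What to change.** Replace the quantile regression with a group × baseline BMI interaction in the two-level mixed model already planned, with school as the upper level. Enter baseline BMI as quartiles or as the planned weight-status categories, or as a flexible continuous term; a linear term alone should not be relied on (step 2). Report the interaction with its confidence interval, and the intervention effect in each baseline BMI group beside it, labelled exploratory.

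If quantile regression is kept for interest in the distribution of follow-up BMI, describe it as that and remove the reference to baseline quartiles.

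The cost is a change of wording in the protocol or the statistical analysis plan before the data are analysed, with no new data. The drawback is low power: with an SE 2.3 to 2.8 times that of the overall effect under the assumed shares, a non-significant interaction should not be read as showing equal effects, and the confidence interval should carry the interpretation.

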### Sample size calculation

Dietary intake of unhealthy foods is the primary outcome. In our previous study [10], the intake of unhealthy foods was 1.7 ± 2.0 portions/day. We now aim for a difference in intake of unhealthy foods of 0.8 portions/day between the intervention and the control group. Sample size calculation was done according to Twisk [68]. With a power of 80% and significance level of 5% and an intra-class correlation coefficient of 2% (clustering at school level), we need to recruit at least 17 schools with 15 children in each school, 255 children in total.

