**Methods:**

Effectiveness of the intervention is compared to standard care within school health services. The 6-month programme, based on Social Cognitive Theory, consists of four components: 1) Health information to parents regarding the child; 2) Motivational Interviewing with the parents by the school nurse concerning the child; 3) classroom activities for the children by teachers; and 4) a web-based self-test of type-2 diabetes risk by parents. Effects will be studied in a cluster randomised trial including 17 schools and 352 six-year old children. The primary outcome is dietary intake of indicator foods, and secondary outcomes are physical activity, sedentary behaviour and BMI. Outcomes will be measured at baseline, at 6 months directly after the intervention, and at follow-up 18 months post baseline. Statistical analysis will be by mixed-effect regression analysis according to intention to treat and per protocol. Mediation analysis will be performed with parental self-efficacy and parenting practices. Quantitative and qualitative methods will be used to study implementation in terms of dose, fidelity, feasibility and acceptability. The hypothesis is that the programme will be more effective than standard care and feasible to perform in the school context.

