#### Primary outcomes

The primary outcome is intake at home of a composite score of indicator foods of importance for energy-balance and health, namely fruit and vegetables (healthy foods) and unhealthy foods (sweets, ice cream, buns/cakes, crisps) and unhealthy drinks high in added sugar (sugar-sweetened beverages). Intake of indicator foods was chosen as the primary outcome because our previous studies in comparable population samples showed that diet was a discriminating factor between different socioeconomic and ethnic groups [6] and also improved as a result of the intervention [10, 12]. Intake will be assessed using food frequency questionnaire, the Children’s Eating Habits Questionnaire (CEQ) which measures intake retrospectively in the home during the preceding month, and shows good reliability [52]. This food frequency instrument has been specifically designed for parents of children aged 2–11 years in eight European countries including Sweden and aims to investigate dietary behaviour and the family food environment. In addition, a revised version of the Eating and Physical Activity Questionnaire (EPAQ) will be used [53]. It measures the child’s intake of indicator foods in the home environment during the previous week, and is a semi-quantitative food frequency questionnaire, and includes portion size both in written text and in pictures. The original EPAQ measured intake during the previous day only and was validated against a 24-h recall in an Australian setting with parents of two to five-year-old children [53]. We will also use a new smartphone-based method to estimate the intake of indicator foods eaten at home (volume and frequency) prospectively through standardised photos taken by parents over two weekdays and one weekend day. This method constitutes a further development of the method developed by Delisle et al. [54]. Newer technology-based methods show promise for improving the accuracy of food records [55]. A relative validation study will be conducted in parallel during baseline, where all methods will be compared to multiple 24-h recalls conducted by independent dietitians as the reference method. Our intention is to use the photo-based method for the primary outcome in the intervention study if shown to be valid. The EPAQ will be used for comparison with our previous studies [10, 12].

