## Discussion

This multi-disciplinary theory-based programme will fill a large knowledge gap regarding evidence-based practice within school health services to promote health-related behaviours and prevent overweight and obesity in children. The programme has been designed to be fully integrated into the usual school routines, making it highly sustainable once the necessary support from the school management can be secured. Taking a universal approach yet tailored to the special needs of families, the programme will have high external validity and with the potential to reduce social inequalities in health. The project will also for the first time establish a link between the school health services and primary health care, thus reaching the whole family. Measures to prevent obesity and T2D are especially important in areas with low SEP where obesity is several-fold higher, and where T2D starts 6–8 years earlier among adults than in high-income areas [15].

One of the study’s strengths is the well-developed programme theory and the description of the hypothetical mechanism of change as well as the strong study design. Furthermore, MI fidelity will be monitored and reported. A number of studies have used MI to target parents regarding children’s diet and physical activity and prevention or treatment of overweight and obesity [69–72] with mixed success. However, none of these reported fidelity to MI. In the present study we will train school nurses well ahead of the intervention and follow their learning process. In additional studies we will relate their MI competence to the effectiveness of the intervention.

The main weakness of the study is that the primary outcome (dietary intake of indicator foods in the home environment) is based on self-report as are the theory-based mediators. Assessing diet, especially in children, remains extremely challenging due to lack of feasible objective methods. We intend to use and validate a photo-based method to estimate selected food items and quantities within this study. We hope that this method will be acceptable to the target group of culturally diverse families many of whom have a low level of education. As a backup method we will use the Child Eating Habits Questionnaire EQ [73] developed collaboratively in eight European countries.

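### The protocol names two different primary outcomes, and the 80% power statement applies only to unhealthy foods, not to the composite declared as primary

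*Protocol article*

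**What the plan says.** Four places in the protocol article state the primary outcome.

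- **Abstract, Methods:** "The primary outcome is dietary intake of indicator foods".
- **Primary outcomes:** "The primary outcome is intake at home of a composite score of indicator foods of importance for energy-balance and health". The components listed are fruit and vegetables (labelled healthy), four kinds of unhealthy food (sweets, ice cream, buns/cakes, crisps) and, as a further item, "unhealthy drinks high in added sugar (sugar-sweetened beverages").
- **Discussion:** among the weaknesses, "the primary outcome (dietary intake of indicator foods in the home environment) is based on self-report".
- **Sample size calculation:** "Dietary intake of unhealthy foods is the primary outcome".

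The sample-size section then plans on unhealthy foods alone: 1.7 ± 2.0 portions/day in the group's previous study, a target difference of 0.8 portions/day, 80% power, 5% significance and an intra-class correlation of 2%, giving 17 schools of 15 children, 255 in all. Study design reports that 352 children were measured at baseline.

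Table 1 lists fruit/vegetable intake and unhealthy-food intake as two separate short-term outcomes. It has no composite and no separate entry for drinks.

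**The concern.** Unhealthy foods are one part of the composite, not the same variable. The composite adds fruit and vegetables, where higher intake is favourable, and perhaps drinks. A difference and an SD in portions/day of unhealthy foods therefore do not carry over to it.

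Two things are at stake. First, whichever variable gives the clearer result could be reported as primary, with support from the protocol's text. That matters more than usual here: registration was retrospective, and the Discussion acknowledges that the outcome is self-reported by families who cannot be blinded once the intervention has started. Second, a reader who takes the composite as primary will assume the trial was planned with 80% power for it, and the article contains no such calculation.

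The place of sugary drinks is a smaller ambiguity. The Primary outcomes section lists them apart from unhealthy foods, while Table 1 has no row for them, so the label unhealthy foods may or may not cover them.

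**Working it through.** **1. Reproducing the stated sample size.** Inputs from the sample-size section: SD 2.0 (reading the ± figure as an SD), difference 0.8, power 80%, significance 5% (taken as two-sided), ICC 0.02, 15 children per school.

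- Per arm, unclustered: 2 × (1.96 + 0.8416)² × 2.0² / 0.8² = 98.1, rounded up to 99; 198 in total.
- Design effect: 1 + (15 − 1) × 0.02 = 1.28.
- Total: 198 × 1.28 = 253.4 children; 253.4 / 15 = 16.9 schools, so 17 schools × 15 = 255.
- A one-sided test would need only 199.7 children, so the stated figure is two-sided.
- Power at 255 with 8 v 9 schools: effective sizes are 8 × 15 / 1.28 = 93.75 and 9 × 15 / 1.28 = 105.5. The standard error is 2.0 × √(1/93.75 + 1/105.5) = 0.284. The ratio is 0.8 / 0.284 = 2.82, and power is Φ(2.82 − 1.96), about 80.5%.

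The arithmetic is sound for unhealthy foods, and every input belongs to that variable.

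**2. What would be needed for the composite.** At 255 children and ICC 0.02, 80% power requires a standardised difference of (1.96 + 0.8416) × √(4 × 1.28 / 255) = 0.397 SD. For unhealthy foods the plan has 0.8 / 2.0 = 0.40 SD. For the composite the article gives no SD, no target difference and no ICC, so whether it reaches 0.40 SD cannot be determined.

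**3. Illustration under assumed inputs.** None of the following assumptions is in the article: the composite is scored as fruit/vegetables minus unhealthy foods; the two parts are uncorrelated; the fruit/vegetable SD *s* is 1.0 to 2.0 portions/day; only unhealthy foods change, by 0.8; the ICC stays at 0.02; the split is 8 v 9 schools. The composite SD is then √(2.0² + *s*²). With 352 children, the mean school size is 352 / 17 = 20.7 and the design effect is 1 + 19.7 × 0.02 = 1.394.

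| *s* | Composite SD | Standardised difference | Power, 255 children | Power, 352 children |
|---|---|---|---|---|
| 1.0 | 2.24 | 0.36 | 71% | 81% |
| 1.5 | 2.50 | 0.32 | 62% | 72% |
| 2.0 | 2.83 | 0.28 | 51% | 61% |

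For unhealthy foods alone, power with 352 children is about 89%. If fruit/vegetable intake also rises by 0.2 to 0.4 portions/day, composite power over the same SDs runs from about 70% to 97% at 255 and about 80% to 99% at 352. All figures are before attrition and ignore the gain from the planned adjustment for baseline values.

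**The case against.** The strongest reply is that this is a loose sentence and not a competing definition. Three of the four statements agree on indicator foods, unhealthy foods are a component of the composite, and basing a sample size on the best-documented component is common. The Data analysis section specifies one model for all outcomes and leaves detail to a separate analysis plan. Recruitment also exceeded the target, at 352 against 255.

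Much of this stands. The conflict concerns the variable, not the analysis model, and powering on a component is acceptable if the protocol says so. It does not say so; it calls the component the primary outcome. A later analysis plan can define the scoring, but it cannot make both sentences true.

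A reader might infer several stronger points that the article does not support:

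- **That the trial is underpowered for the composite.** The illustrative powers rest on assumed SDs, correlation and effects, and they range from 51% to 99%. They show that power is unknown.
- **That favourable changes would cancel in an unsigned sum.** Nothing says the items are summed without regard to direction. The article labels them healthy and unhealthy, and scoring is properly left to the analysis plan.
- **That drinks are excluded from the powered variable.** The separate listing suggests it and Table 1 points the other way, so the term is only ambiguous.
- **That the dietary instruments cannot deliver portions/day, so the named backup questionnaire should be replaced.** The intended photo method records volume and frequency. That the backup lacks portion size could be inferred only from the silence of a short description.

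**Conclusion.** The point holds as an internal contradiction with a definite consequence. The sample-size section names unhealthy foods as primary; the Primary outcomes section names a composite, and the Abstract and Discussion also refer to indicator foods. The 80% power at 255 children is correct for unhealthy foods and does not attach to the composite. It would carry over only if the composite's standardised difference were also about 0.40 SD at the same ICC, which the article neither states nor lets a reader derive.

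The contradiction and the missing composite inputs rest on the text alone. The power figures for the composite rest entirely on the assumptions listed with them. The matter should be settled before outcome data are analysed, because it decides which result counts as the trial's primary finding.

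**What to change.** Before outcome data are analysed, name one primary variable identically in the Abstract, Primary outcomes, Sample size calculation and Discussion, align Table 1 with it, and state whether sugar-sweetened drinks are part of it. Either of two routes resolves the conflict:

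1. Make intake of unhealthy foods at home, in portions/day, the primary outcome, since it is the powered variable, and move the composite and fruit/vegetable intake to secondary outcomes.
2. Keep the composite as primary, state that the sample size was set on its unhealthy-foods component, and restate power for the composite from its blinded baseline SD and the 352 children measured, with an explicit target difference.

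The cost is wording and, on the second route, one recalculation; no new data are needed. The drawback of the first route is that the composite loses primary status. The drawback of the second is that the restated power may be less favourable than 80%.

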### Study design

The Healthy School Start Plus study will be conducted as a cluster-randomised parallel trial with randomisation at school level, with a wait-list control group. Simple randomisation of schools to the intervention or control group with a 1:1 allocation ratio was done using a computer-generated randomisation procedure by a statistician not involved in the study. As all school nurses in the intervention group had to undergo training in Motivational Interviewing (MI), something that takes a few months to reach a certain level of competence, randomisation took place before the baseline measurements in order to allow time for this training. However, allocation of schools to intervention or control was only revealed to headmasters, school nurses and the project leader, until baseline measurements done by research assistants, were finalised. Only then were teachers and parents informed. Baseline data was collected in September–October 2017 (T0) from 352 children. Data will again be collected 6 months after the baseline at the end of the intervention in April–May 2018 (T1) and at follow-up in April–May 2019 (18 months post baseline, T2). As an incentive to retain participants in the study, each family will receive a coupon for a healthy meal at a shopping centre restaurant. Mediators will also be measured on one occasion during the intervention, in February 2018 (TM). After the T2 measurement the control schools will be offered the intervention, including MI-training of the school nurses.

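### The 255 children to be recruited carry no allowance for few clusters, unequal schools or loss; on the protocol's own inputs they give about 75% power, not 80%

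*Protocol article*

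**What the plan says.** The Sample size calculation section takes its SD from the previous trial, where "the intake of unhealthy foods was 1.7 ± 2.0 portions/day", and aims for a "difference in intake of unhealthy foods of 0.8 portions/day between the intervention and the control group". It assumes 80% power, a 5% significance level and an "intra-class correlation coefficient of 2% (clustering at school level"), cites a textbook method, and concludes that "we need to recruit at least 17 schools with 15 children in each school, 255 children in total". It mentions no degrees-of-freedom correction, no variation in school size and no loss to follow-up.

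The Study design section describes "Simple randomisation of schools to the intervention or control group with a 1:1 allocation ratio", with outcomes at 6 and 18 months after baseline. The Abstract describes "a cluster randomised trial including 17 schools and 352 six-year old children". The Data analysis section plans a two-level mixed model adjusted for the baseline value, with multiple imputation of missing data, and leaves the detail to a later statistical analysis plan.

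**The concern.** Three simplifications are built into the 255.

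- It uses normal quantiles, although the treatment contrast rests on only 17 randomised units.
- It uses one common school size of 15.
- It is given as a number to recruit, yet it equals the number needed in the analysis.

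The protocol itself expects response problems. It plans weekly questionnaire reminders and a retention incentive, and its Discussion mentions differential response. If the simplifications matter, the stated 80% is not the power that the stated recruitment delivers, and a neutral result would be read against too favourable a figure.

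**Working it through.** **Inputs from the protocol.** Difference 0.8 portions/day, SD 2.0, ICC 0.02, 15 children per school, 17 schools, 5% significance, 80% power. Sidedness is not stated; two-sided reproduces the figure, while one-sided gives 198 children and does not. The most balanced split of 17 schools is 8 against 9.

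**Assumed inputs.** Loss rates of 10%, 20% and 30%, and a coefficient of variation (CV) of school size of 0.4. The document gives neither. The baseline correlation r is also not given; r = 0 below unless stated.

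**Step 1: reproduce the stated figure.**
- Per arm without clustering: 2 × (1.96 + 0.8416)² × 2.0² / 0.8² = 98.1.
- Design effect: 1 + (15 − 1) × 0.02 = 1.28.
- Total: 2 × 98.1 × 1.28 = 251.2. Dividing by 15 gives 16.7 schools, rounded up to 17, hence 255.
- Slack: 255 / 251.2 = 1.015, about 1.5%.

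The formula is applied correctly. The result leaves essentially nothing for loss, unequal sizes or few clusters.

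**Step 2: the same inputs with 17 clusters.**
- SE = 2.0 × √(1.28/120 + 1.28/135) = 0.284; noncentrality = 0.8 / 0.284 = 2.82.
- Normal reference (critical value 1.96): power 80.5%.
- t reference with 17 − 2 = 15 df (critical value 2.13): power 75.0%.
- Schools of 15 needed for 80% with t: 19 (80.2%).
- Simple randomisation does not guarantee 8/9. A 7/10 split gives 73.8% and a 6/11 split gives 71.3%.

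**Step 3: loss from 255 recruited (8/9 split, equal sizes).**

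| Assumed loss | Children per school | Normal | t(15) |
|---|---|---|---|
| 0% | 15 | 80.5% | 75.0% |
| 10% | 13.5 | 77.2% | 71.5% |
| 20% | 12 | 73.3% | 67.5% |

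The shortfall from loss appears even with normal quantiles.

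**Step 4: the 352 enrolled (352/17 = 20.7 per school), t(15), 8/9 split.** The design effect for unequal sizes is 1 + ((1 + CV²) × m − 1) × 0.02, where m is the mean number analysed per school.

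| Assumed loss | Equal sizes | CV 0.4 |
|---|---|---|
| 0% | 84.2% | 82.5% |
| 10% | 81.5% | 79.8% |
| 20% | 78.1% | 76.5% |
| 30% | 73.9% | 72.4% |

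With equal sizes, 80% needs about 301 analysed children, so it survives up to about 14% loss (1 − 301/352). With equal sizes, the difference detectable with 80% power is 0.76 portions/day with no loss and 0.82 at 20% loss.

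**Step 5: baseline adjustment.** Multiplying the SD by √(1 − r²), 17 × 15 with t(15) and no loss gives 78.8% at r = 0.3, 80.3% at r = 0.35 and 86.0% at r = 0.5. With 20% loss, r = 0.5 gives 79.6%.

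**The case against.** The strongest reply has four parts.

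**The arithmetic is right.** A reader might infer a calculation error. There is none: the simple formula yields 251.2, and 255 follows. What fails is the power claim attached to the number, because the formula ignores the small number of schools and any loss.

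**The trial enrolled 352, not 255.** Loss would have to exceed 27.6% (1 − 255/352) before fewer than 255 children remained. This stands and shrinks the practical effect considerably; 75% and 67.5% do not describe the enrolled sample. Nor is it an error that a paragraph recording an advance calculation still shows 255, since the enrolled number is given elsewhere in the article.

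**The planned analysis adjusts for baseline, while the calculation uses the unadjusted SD.** This also stands. A correlation of about 0.35 would restore 80% at 17 × 15 with no loss. But the section gives no correlation and claims no such credit, so the gain cannot be counted on.

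**The choice of degrees of freedom belongs in the SAP.** It does. A reader might go on to infer that the mixed model will be tested against 1.96 and so exceed 5% type I error. The protocol names no reference distribution, so it does not support that. The power figure is different: it is stated here and can be checked here.

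**Conclusion.** The point holds for the stated power. On the protocol's own difference, SD and ICC, 17 schools of 15 give about 75% with t on 15 df, an 8/9 split, equal sizes and complete data. That is about five points below the stated 80% and needs no assumed loss rate or size variation; it does take the outcome as unadjusted for baseline. Because 255 is a recruitment number, any loss widens the gap.

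For the 352 enrolled, power is 84% with no loss. It falls to between 74% and 81.5% over an assumed 10% to 30% loss with equal schools, and is a point or two lower at a size CV of 0.4, all before any gain from baseline adjustment. Every figure below 80% for the enrolled sample therefore rests on assumed loss, with or without assumed size variation, and on r = 0. It would be too strong to conclude that the trial is underpowered; whether it keeps 80% depends on retention, school sizes and baseline correlation, none of which the article gives.

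**What to change.** Keep the 255 as the record of the advance calculation, and say that it assumes normal quantiles, equal schools and complete data. Beside it, state power and detectable difference for the 17 schools and 352 children enrolled. Use t with 15 df, the actual arm split and school sizes, a retention range such as 70–90% at each follow-up and, if known, the baseline correlation. In the SAP, name a small-sample df method for the group effect (Kenward-Roger or Satterthwaite) so that the test matches the power statement.

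The cost is one rewritten paragraph and one model option. The quoted power may become somewhat less favourable. Recruitment and conduct do not change.
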